| Recruitment/Carrying out interview                                                                                                                                      | Psychological Distress/Risk from disclosure                  | Researcher: stress arising from listening to distressing disclosures | Researchers are experienced in working with people with mental health problems. Interviewers are encouraged to discuss any issues with their line manager. All researchers are appropriately qualified with adequate experience. Adequate training e.g. Good Clinical Practice. Regular debriefs with PI. Counselling offered as needed | Low                      | A                   |
| Duration of interview and afterwards                                                                                                                                    | Risk from distress from disclosure                           | Interviewee: risk of distress                                        | Researchers are experienced in working with people with mental health problems and will have information regarding support they can pass on to interviewees. Protocols are in place for contacting clinical lead for study ([name]) who will liaise with support services.                                                        | Low                      | A                   |

| Date: (1)
2 nd April 2014                                                                                                                                 | Assessed by: (2)
[name]
[name] | Checked/Validated by: (3)
[name] (02.04.2014)                                                                       | Location: (4)
Face-to-face
interviews/assessment/observati
ons in NHS settings and
participant homes and
telephone interviews | Assessment ref
no (5) | Review
date: (6) |
|-------------------------------------------------------------------------------------------------------------------------------------------------------------------------|--------------------------------------------------------------|-------------------------------------------------------------------------------------------------------------------------------|----------------------------------------------------------------------------------------------------------------------------------------------|--------------------------|---------------------|
| Task / premises: (7)
Researchers carrying out interviews/assessments/observations with service users and carers at the University and in NHS and community settings. |                                                              |                                                                                                                               |                                                                                                                                              |                          |                     |
| Activity (8)                                                                                                                                                            | Hazard (9)                                                   | Who might be harmed and how (10)                                                                                              | Existing measures to control risk (11)                                                                                                       | Risk rating (12)         | Result (13)         |
| Working with NHS Staff/Patients                                                                                                                                         | Identifying bad practice                                     | Researcher

Impact on project/results/data collection/damage to reputation of staff/project/School/University/ NHS Unit | Action to be taken in this event covered by study protocol – Regular meetings with PI                                                        | Low                      | A                   |

| Date: (1)
2 nd April 2014                                                                                                                                 | Assessed by: (2)
[name]
[name] | Checked/Validated by: (3)
[name] (02.04.2014)                                          | Location: (4)
Face-to-face
interviews/assessment/observati
ons in NHS settings and
participant homes and
telephone interviews                                                                                                                                                                                                                                                                                                                                                                                                                                       | Assessment ref
no (5) | Review
date: (6) |
|-------------------------------------------------------------------------------------------------------------------------------------------------------------------------|--------------------------------------------------------------|--------------------------------------------------------------------------------------------------|------------------------------------------------------------------------------------------------------------------------------------------------------------------------------------------------------------------------------------------------------------------------------------------------------------------------------------------------------------------------------------------------------------------------------------------------------------------------------------------------------------------------------------------------------------------------------------|--------------------------|---------------------|
| Task / premises: (7)
Researchers carrying out interviews/assessments/observations with service users and carers at the University and in NHS and community settings. |                                                              |                                                                                                  |                                                                                                                                                                                                                                                                                                                                                                                                                                                                                                                                                                                    |                          |                     |
| Activity (8)                                                                                                                                                            | Hazard (9)                                                   | Who might be harmed and how (10)                                                                 | Existing measures to control risk (11)                                                                                                                                                                                                                                                                                                                                                                                                                                                                                                                                             | Risk rating (12)         | Result (13)         |

| Task / premises: (7)
Researchers carrying out interviews/assessments/observations with service users and carers at the University and in NHS and community settings. |                                                              |                                                          |                                                                                                                                                                                       |                          |                     |
| Activity (8)                                                                                                                                                            | Hazard (9)                                                   | Who might be harmed and how (10)                         | Existing measures to control risk (11)                                                                                                                                                | Risk
rating
(12)   | Result
(13)      |
| Clerical/Computer Work                                                                                                                                                  | DSE related                                                  | Research Staff

RSI/musculoskeletal pain injuries. | Covered by Health & Safety Induction and Policy Documents

www.nursing.manchester.ac.uk/intranet/about/hs/ | Low                      | A                   |

| Date: (1)
2 nd April 2014                                                                                                                                 | Assessed by: (2)
[name]
[name] | Checked/Validated by: (3)
[name] (02.04.2014)                                                              | Location: (4)
Face-to-face
interviews/assessment/observati
ons in NHS settings and
participant homes and
telephone interviews | Assessment ref
no (5) | Review
date: (6) |
|-------------------------------------------------------------------------------------------------------------------------------------------------------------------------|--------------------------------------------------------------|----------------------------------------------------------------------------------------------------------------------|----------------------------------------------------------------------------------------------------------------------------------------------|--------------------------|---------------------|
| Task / premises: (7)
Researchers carrying out interviews/assessments/observations with service users and carers at the University and in NHS and community settings. |                                                              |                                                                                                                      |                                                                                                                                              |                          |                     |
| Activity (8)                                                                                                                                                            | Hazard (9)                                                   | Who might be harmed and how (10)                                                                                     | Existing measures to control risk (11)                                                                                                       | Risk rating (12)         | Result (13)         |
| Research Governance                                                                                                                                                     | Non-Compliance                                               | Research Staff

Damage to reputation of staff/project/School/University.

Potential disciplinary action. | Research Study Monitoring Self-Assessment Form. Research Governance Policy and Procedure.                                                    | Med                      | A                   |

| Action plan (14) |                                                                                                                                                                               |                                      |                           |             |
|-------------------------|-------------------------------------------------------------------------------------------------------------------------------------------------------------------------------|--------------------------------------|---------------------------|-------------|
| Ref No           | Further action required                                                                                                                                                | Action by whom                | Action by when     | Done |
| 1                       | Lone Worker risk assessment to be reviewed and modified as project develops in line with any changes                                                                          | [name]                        | Sept 2014                 |             |
| 2                       | Lone worker to be given training/training information for use of Lone Worker Device (contact [contact] ) | [name]/
Programme Manager | June 2014                 |             |
| 3                       | Shared calendar or similar set up and filled in regularly informing PI/appointed research staff member of any visits                                                          | [name]/
Programme Manager | June 2014, then as needed |             |
| 4                       | Assessment of residential areas ensuring high risk areas are identified                                                                                                       | [name]/
Programme Manager  | As needed                 |             |
| 5                       | Escalation procedure devised with PI                                                                                                                                          | [name]/
Programme Manager  | June 2014                 |             |

## Appendix 3: Lone worker policy

1

### **School of Nursing, Midwifery & Social Work Safety Guidance for Research Fieldwork in the UK**

#### **Summary of Responsibilities of PI who have research staff doing fieldwork**

- Ensure the '**SNMSW Safety Guidance for Research Fieldwork**' is provided to research staff and this is read and understood by the researcher;
- Complete the **SNMSW Lone Worker Risk Assessment Form** (provided in Appendix 1 of the Safety Guidance and also available on School's Staff Intranet (<http://www.nursing.manchester.ac.uk/intranet/researchadministration/>);
- Ensure that immediate access to 'Contact details' including details about the person to contact in case of emergency and agreed fieldwork contact plan is available out of hours;
- Ensure the researcher is clear on who to provide details of fieldwork visits to (this may involve having access to a shared/password protected calendar);
- Ensure cover arrangements are provided by the PI when on holiday or away from the University;
- If study involves fieldwork with individuals who pose a 'higher risk', please complete the Risk Assessment Questionnaire for high risk studies and modify original Lone Worker Risk Assessment provided in Appendix 2 of the Safety Guidance; also available on School's Intranet (<http://www.nursing.manchester.ac.uk/intranet/researchadministration/>)
- Mandatory use of Rocksure Peoplesafe Lone Worker Unit. (<http://www.nursing.manchester.ac.uk/intranet/researchadministration/researchersafety>)

**Please ensure that PIs and researchers adhere to the 'Flowchart of process for monitoring lone working (Research Fieldwork)'**

SNMSW Safety Guidance Research Fieldwork April 2014

## **Appendix 4: Distress policy**

### **EQUIP Distress Protocol**

If a participant appears to become distressed, the researcher will:

- Encourage the participant to take a break from answering questions.
- Acknowledge that talking about/answering questions about problems can be distressing.
- Offer support by reassuring the service user that they do not need to answer a question(s) if they do not wish to.
- Ask if they would like to continue with the interview/completing questionnaires or prefer to stop.

If they prefer to stop then:

- Finish the interview/questionnaire completion and offer to return at another time.
- If the service user withdraws their consent to participate in the study then this must be communicated to the work stream lead or Programme Manager.

If the interview continues:

- Take time at the end of the meeting to talk informally, and encourage service users to access further support dependant on their level of distress. This may be to visit their GP or mental health service provider or refer service users to list of support agencies on the information sheet.
- If the service user has any questions or requires reassurance about the research they should be encouraged to contact the work stream lead or Programme Manager (details on Debriefing Sheet and Participant Information Sheet).
- If the participant still appears to be distressed when the interview is over then the researcher will offer to phone back in a couple of days to ensure the distress has not escalated and to reiterate the sources of support. If this is the case or there is a perceived risk of harm to self or others the site Clinical Lead will also be informed and a decision made on contacting the relevant authorities in line with the EQUIP risk protocol.

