### ***Study 5***

Completing the measures is not perceived as being high risk but there is always a risk that service users/carers may become distressed when thinking about difficult personal experiences. This risk has been assessed in the overall risk assessment for the work stream and as a result sources of further support will be included at the end of the questionnaires to ensure that participants have access to a source of support should they require it. This information will also be provided in participant information sheets

Data collection may require the researcher to visit participants at their work places or their homes. The School of Nursing, Midwifery and Social Work's Lone Worker Policy (Appendix 3) will be employed, as well as project specific risk assessment (Appendix

2). These involve research staff leaving details of their visits with a supervisor who they contact before and after the visit and using 'PeopleSafe' technology. When NHS CSOs carry out data collection they will follow their NHS Trust lone worker policies.

There is a risk to researchers that they might become distressed when collecting sensitive data within questionnaires. This has been assessed as a low risk but interviewers will have access to their supervisors for support on a regular basis and as required. NHS CSOs will have access to their supervisors within the NHS for support as well as regular contact with the EQUIP Programme Managers and Clinical Leads.

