### *Informing potential participants of possible risks and anticipated benefits*

All potential participants will be provided with an information sheet written to current NRES guidelines and favourably reviewed by the relevant ethics committee, prior to the study commencing. Service users and carers have been involved in developing the participant information sheets to ensure they are accessible. The information sheet will be provided to potential participants at the point of them expressing an interest in participating. It will provide potential participants with information about the study, including the potential benefits and risks of taking part, confidentiality and the right to withdraw as described above. Researcher contact details will be provided so participants can contact them with any queries prior to the participant deciding to take part. Researchers will further discuss risks and benefits immediately prior to the data collection taking place.

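### Appendix 4 lists the closing talk, the call-back offer and the Clinical Lead step only for participants who continue, not for those who stop (minor; participant safety only)

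*Protocol*

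**What the plan says.** Protocol Appendix 4 (EQUIP Distress Protocol) begins with four steps for any participant who becomes distressed: a break, acknowledgement, reassurance ("Offer support by reassuring the service user that they do not need to answer a question(s) if they do not wish to") and a choice between going on and stopping. It then divides.

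- **Stop branch, two bullets.** The researcher is to "Finish the interview/questionnaire completion and offer to return at another time". Any withdrawal of consent is to be reported to the work stream lead or Programme Manager.
- **Continue branch, three bullets.** The first begins "Take time at the end of the meeting to talk informally" and goes on to signposting. The second says whom to contact with questions about the research. The third opens "If the participant still appears to be distressed when the interview is over" and says that "the researcher will offer to phone back in a couple of days"; it also says when the site Clinical Lead is brought in, including where "there is a perceived risk of harm to self or others the site Clinical Lead will also be informed".

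No closing section applies to both branches.

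**The concern.** After-care is tied to the wrong condition. Stopping is, if anything, a sign of greater distress, yet a researcher following the headings would give that person no closing talk and no offer of a call-back. Nothing in the protocol argues for such a difference. The Study 7 text on semi-structured interviews, under Governance and Ethical issues, gives the purpose of Appendices 4 and 5 as support during participation and afterwards, where needed.

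Participants have severe mental illness, and data collection may take place in their homes. The appendix covers questionnaire completion as well as interviews, and the Study 7 text on observation sends distressed participants to the same policy. What is at stake is participant safety. Sample size, outcomes, estimation and error rates are not touched.

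**Working it through.** No calculation applies beyond a count. The check sets the branches of Appendix 4 against each other and then against the protocol's other text on distress.

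**Count of bullets in Appendix 4.** 4 common + 2 stop + 3 continue = 9. Of the three after-care steps at issue (closing talk, call-back offer, Clinical Lead step), 0 of 3 appear in the stop branch and 3 of 3 in the continue branch.

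**What else covers a participant who stops?**

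| Place in the Protocol | What it supplies | What it does not supply |
|---|---|---|
| Governance and Ethical issues, Study 5 | Sources of support at the end of the questionnaires, and "This information will also be provided in participant information sheets" | A talk or a call-back; someone who stops midway may also not reach the end of the questionnaire |
| Informing potential participants of possible risks and anticipated benefits | Timing of the sheet: "The information sheet will be provided to potential participants at the point of them expressing an interest in participating" | Anything at the time of distress, since the sheet comes earlier |
| Study 7, Semi-Structured In-Depth Interviews | Onward disclosure where serious harm is suggested in an interview | Cover for distress without such a disclosure, or for Study 5 |
| Appendix 2, Risk Assessment, row on the interview and afterwards (Studies 5 and 7) | Support information that researchers can pass on, and a route to the clinical lead, with no stop or continue condition | A talk or a call-back |

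Signposting and escalation are therefore partly covered for people who stop. The talk and the call-back are not: 2 elements remain without a counterpart.

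**Is the split intended?** The call-back condition is "If the participant still appears to be distressed when the interview is over". An interview that was stopped is also over. Perceived risk of harm, likewise, does not depend on the interview having gone on. Both triggers make sense in either branch, which points to a heading in the wrong place and not to a deliberate rule. This is an inference from the wording.

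**A second wording point in the same bullet.** After the call-back offer, the text makes informing the Clinical Lead depend on a condition introduced only by a pronoun. It can mean that the participant is still distressed at the end, or that distress is found to have escalated at the call-back. Perceived risk of harm triggers the Clinical Lead on either reading. Alone, this would be no more than a missing detail.

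**The case against.** The strongest reply is that this is a layout slip which a sensible reader corrects. The last bullet carries its own triggers, and an experienced researcher would probably apply them to a stopped interview. The protocol says interviewers and their supervisors are experienced in supporting distressed people, Appendix 2 rates interviewee distress as low risk, and the Study 5 text does not regard completing the measures as high risk. The offer to return is a further contact, though its purpose is data collection. Escalation for people who stop has a route through Appendix 2. The stated aim is conditional, written for Study 7, and assigned to Appendices 4 and 5 together. Neither the Appendix 5 debriefing sheet nor the EQUIP risk protocol is in the text available, and either may supply what Appendix 4 leaves out.

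Most of this stands, and it bears on weight. It justifies the lowest grade. It means that confidence is high about where the bullets are printed and lower about whether after-care would be missing in practice. It does not make the page right: a written procedure should not rely on staff reading against its headings, and no other text available supplies the talk or the call-back for someone who stops.

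**Conclusion.** The concern holds, as a cheap improvement at the lowest grade. Taken literally, Appendix 4 gives a participant who stops less after-care than one who continues, and that sits badly with the stated aim of support during and after participation. The uncovered part is two elements, the closing talk and the call-back offer. The person who stops still receives the four common steps, the offer to return, and the partial cover in the Study 5 and Study 7 governance text and in Appendix 2.

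The conclusion rests on the text available, without Appendix 5 or the EQUIP risk protocol. The protocol gives no rate of distress or of stopping, so no number of participants affected is claimed. There is no consequence for the statistical analysis.

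**What to change.** In Appendix 4, keep the two stop bullets as they are. Move the three bullets now in the continue branch under a common heading, such as 'However the contact ends'. In the last of them, replace the ambiguous condition with the event meant: still distressed at the end of contact, or distress escalated at call-back. That choice belongs to the sponsor's clinical leads.

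The cost is a one-page edit, a short briefing for researchers and, if they have been following the headings literally, a few more call-backs. No new staff or procedures are needed.
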